### Interim analyses {21b}

Interim analysis will be performed 1 year after the surgery of the final randomised participant. There will be no formal criteria for trial termination; however, if it is observed that the intervention is associated with significant harm to subsequently enrolled participants, then consideration of trial termination will be conducted.

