### Outcomes {12}

#### Primary outcome

The primary outcome will be the side-to-side difference in anterior tibial translation as measured on the GNRB arthrometer at 2 years post-operatively, between groups. Maximum anteroposterior tibial translation at 134 N will be recorded on both the operative and non-operative knees pre-operatively and post-operatively at 3, 12 and 24 months. The goals of ACL reconstruction are to restore sagittal and rotatory stability to the knee and to prevent secondary injuries such as meniscal tears, and progression to osteoarthritis [35]. Common means of assessing this is by comparison of pre- and post-operative subjective Lachman manoeuvre and anterior drawer; however, these are often imprecise and subjective [36]. Consequently, devices to accurately measure anterior tibial translation have been developed, most popularly the KT-1000 ™ manual arthrometer (MEDmetric®, San Diego, USA) [37]. However, this device has been criticised for poor inter- and intra-observer reliability, and as such, newer computerised models such as the GNRB (Genourob, Laval, France) have been developed, with improved reliability [38]. Studies have utilised these arthrometers to compare between anterior cruciate ligament surgical techniques, such as graft types [39, 40], assessing post-operative outcomes [41], as well as analysing residual joint laxity after ligament reconstruction [42]. This outcome has been selected due to its ability to assess whether the addition of suture tape in ACLR results in knee stability that is more similar to the contralateral uninjured knee than standard ACLR technique. Anterior tibial translation and knee laxity may vary from individual to individual, and for this reason, side-to-side difference has been chosen as the primary outcome, allowing the contralateral knee to be a within-participant baseline measure, reducing the variability in outcome owing to between participant differences.

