### Recruitment {15}

Recruitment will be conducted continuously across patients eligible until the target randomised sample size is achieved. Based on institutional caseloads, it is anticipated this will take 1–2 years. A dedicated member of the research team will be tasked with recruitment on clinic days, such that all prospective participants are given appropriate opportunity to understand the study before and during involvement.

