### Implementation {16c}

The allocation sequence will be developed by an independent statistician. It will be integrated into the REDCap automated randomisation platform and will be blinded to all other investigators. Enrolment of participants will be overseen by the lead surgeons, and associate investigators ST and LB, and will be carried out by associate investigators LH and EN. Randomisation and assignment to the intervention arm will be performed intraoperatively, following assessment and management of concomitant cartilage and meniscal injuries by the associate investigators LB and ST.

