### Composition of the data monitoring committee, its role and reporting structure {21a}

The Principal Investigator will act as the data manager for the trial. The research team will meet as above in lieu of an official Data Monitoring Committee. Direct access to the data will be granted to authorised representatives from the sponsor, host institution or ethics board for monitoring and/or audit to ensure compliance with regulations.

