## Trial status

The current protocol is Version 1.3, dated 30 August 2021. Recruitment commenced on 03 March 2022. Recruitment is anticipated to finish on 30 June 2024.

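### The only interim analysis falls a year after the last operation, so it cannot serve its stated purpose of protecting participants enrolled later

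*Protocol article*

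**What the plan says.** Interim analyses {21b} plans one interim analysis and fixes its date: "Interim analysis will be performed 1 year after the surgery of the final randomised participant". It sets no formal stopping criteria, but continues: "if it is observed that the intervention is associated with significant harm to subsequently enrolled participants, then consideration of trial termination will be conducted".

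Other sections of the protocol article bear on this:

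- Recruitment {15} sets the end of enrolment: "Recruitment will be conducted continuously across patients eligible until the target randomised sample size is achieved". The target is 66 randomised.
- Implementation {16c} sets the moment of treatment: "Randomisation and assignment to the intervention arm will be performed intraoperatively".
- The primary outcome is the "side-to-side difference in anterior tibial translation as measured on the GNRB arthrometer at 2 years post-operatively", that is, 12 months after the interim for the last participant.
- Trial status gives the dates: "Recruitment commenced on 03 March 2022. Recruitment is anticipated to finish on 30 June 2024". Sample size {14} and Recruitment {15} instead expect one to two years.
- The data monitoring section {21a} says: "The research team will meet as above in lieu of an official Data Monitoring Committee". Section {5d} has that internal committee meet at least monthly, and section {22} has it review adverse events regularly.

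**The concern.** The timing and the purpose in Interim analyses {21b} exclude each other. A look meant to protect people not yet enrolled has to happen while people are still being enrolled. This one is anchored to the final randomised participant and then delayed by a further year. The intervention is a single operation, so stopping at that date could not withdraw treatment from anyone either.

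The date has a second consequence. Judging whether the intervention is associated with harm requires results by arm, and at that date part of the cohort still awaits its primary measurement. The section does not limit the look to harms. The only monitoring body named is the research team itself. Concealment mechanism {16b} has allocations emailed to members of that team, and Participant timeline {13} allows a research-team member to take GNRB measurements. The article should therefore say what the look covers and who sees it.

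**Working it through.** The plan gives no figure for this point, so there is none to reproduce. The check is a matter of dates.

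**Step 1: can the look protect later enrolees?** Let T be the date of the final randomised participant's surgery.

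- Randomisation is intraoperative and stops at the target, so all 66 are randomised and operated on by T.
- The interim is at T + 12 months.
- Participants randomised after the interim: 66 − 66 = 0.
- Shortest time since surgery at the interim: 12 months.

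Study setting {9} allows more than 66 to be recruited, but only so that 66 reach randomisation. That does not change the result.

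**Step 2: how much primary data is still outstanding?** A participant operated on at date s has the 24-month visit at s + 24 months. It is outstanding at the interim if s + 24 > T + 12, that is, if s falls in the last 12 months of accrual. With uniform accrual over R years (R at least 1), the number outstanding is 66 × 1/R.

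- *Trial status dates.* 3 March 2022 to 30 June 2024 is 850 days. The interim falls about 30 June 2025 and the last 24-month visit about 30 June 2026. Participants operated on by 30 June 2023 have reached 24 months: 484/850 = 56.9%, or 37.6 of 66, about 38. Outstanding: 366/850 = 43.1%, or 28.4 of 66, about 28.
- *Recruitment over 2 years.* 66 × 1/2 = 33 outstanding.
- *Recruitment over 1.5 years.* 66 × 1/1.5 = 44 outstanding.
- *Recruitment over 1 year.* 66 × 1/1 = 66 outstanding; nobody has yet reached 24 months.

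These are counts of randomised participants. If the 30% dropout expected in Sample size {14} fell evenly, the counts would shrink but the proportions would stay the same.

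**Step 3: who could see by-arm results?** Set side by side:

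- The research team stands in for a monitoring committee ({21a}).
- Allocation is emailed to members of the research team ({16b}).
- GNRB measurements may be taken by a research-team member or by a physiotherapist ({13}).
- GNRB technicians are to be blinded ({17a}).

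These statements can all be true together, but only if the people who measure are kept apart from those who receive allocations and by-arm results. The article does not state that separation for the interim look.

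**The case against.** The strongest reply is that the termination sentence is general. It speaks of harm being observed and does not say that the observation must come from the interim analysis. The internal committee meets at least monthly and reviews adverse events. Serious events go to the ethics board within 72 hours, apart from listed expected surgical complications. Clinicians outside the investigative team also review events, and the ethics board determines auditing. Termination could therefore be raised at any monthly meeting during recruitment. Section {6b} adds that both procedures are already standard care at the institution.

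Much of this stands. A reader might infer that the trial has no safety oversight able to stop further implantation; the documents do not support that. The 0 of 66 applies to the scheduled interim only. What remains is that the one analysis planned under {21b} cannot do what that section attaches to it, and that the sections on monthly review do not describe a comparison by arm.

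Two other inferences go too far:

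- *Inflated type I error.* Interim analyses {21b} states no efficacy test, and the only decision it mentions concerns harm. A second test of the primary outcome would be the reader's assumption.
- *Unblinding of participants or GNRB assessors.* No route is shown by which aggregate results would reach participants. Section {17a} says the technicians are blinded and notes that the arthrometer applies its force by computer.

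It is also fair to say that a by-arm table during recruitment would be thin. At half of 66, about 16 per arm, 0 against 4 events gives a two-sided Fisher p of 2 × C(16,4)/C(32,4) = 2 × 1820/35960 = 0.10. Such a review would inform judgement; it would not serve as a test.

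**Conclusion.** The point holds as an internal contradiction in Interim analyses {21b}. The scheduled look comes after enrolment has closed and after every operation has been done, so it could spare 0 of 66. This follows from the protocol's own sequence and needs no assumption.

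The look also comes before the primary data are complete. How far before depends on accrual: about 28 of 66 outstanding on the Trial status dates, and 33 to 66 for recruitment lasting two years down to one. These figures assume uniform accrual and that the recruitment dates track the dates of surgery.

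This is a moderate correction to how the safety look is specified. The planned 24-month analysis and its stated assessor blinding are not shown to be compromised.

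**What to change.** Reconcile timing and purpose in Interim analyses {21b} in one of two ways:

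1. Place a harms-only review by arm within the recruitment period, tied to the existing committee meetings and using the adverse events already logged in REDCap under section {22}. Attach the consideration of termination to that review.
2. Keep the look one year after the last surgery, but relabel it as a descriptive harms report and remove the termination purpose.

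In either case add two statements: no between-arm comparison of GNRB or patient-reported outcomes is made before the last 24-month visit, and nobody who takes GNRB measurements sees by-arm results.

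The cost is a few sentences of protocol wording and, for the first option, a short adverse-event table during recruitment. One small downside is that Secondary outcomes has complications recorded from the medical record at 2 years. Any of those that are not also logged as adverse events would need earlier extraction if the review is to include them.

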### Methods for additional analyses (e.g. subgroup analyses) {20b}

Subgroup analysis will be explored to identify possible treatment effect modifying baseline factors such as age, sex, return to sport expectations and pre-operative ipsilateral knee laxity as measured on the GNRB arthrometer.

### Methods in analysis to handle protocol non-adherence and any statistical methods to handle missing data {20c}

All principal analyses will be based on the intention-to-treat principle, analysing participants in the groups to which they are randomised. Missing data will be quantified and if possible multiple imputation will be used; otherwise, simple imputation will be used. Owing to the nature of enrolment and randomisation in this study, it is unlikely that a participant will be randomised and subsequently not receive the intervention, and thus adherence does not apply directly to the intervention arm.

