### Sample size {14}

All statistical methods and power analysis were developed through consultation with an independent statistician. Power analysis was performed with G*power 3.1 Software. To achieve a minimum 80% statistical power with an alpha value of 0.05, power analysis based on a hypothesised mean residual side-to-side difference of 2 mm of anteroposterior tibial translation yielded a sample size of *n*=48 (24 per group) utilising an expected independent *t*-test [47–50]. Although previously published KT-1000 data was utilised for power analysis, it has been shown that the GNRB exhibits similar absolute measures in side-to-side anterior tibial translation to KT-1000 utilised by experienced observers, whilst having reduced scatter around the mean [38]. This would mean that utilising KT-1000 published data to establish a power analysis would be a conservative method, and likely over-estimate the required sample size to detect significant differences.

Secondary power analysis based on 2-year IKDC total scores yielded a total sample size of 48 (*n*=24 in each group) to detect significant differences with 80% power and an alpha value of 0.05 with an anticipated independent sample two-tailed *t*-test. This is based on a previous retrospective study of suture-tape ACL reconstruction which reported a mean change from baseline IKDC of 56 ± 17 in SA-augmented ACLR, compared with 38 ± 25 in conventional ACLR [29, 51]. Secondly, previous studies evaluating the IKDC [51] which reported that a change score of 12.8 points would be sufficient to detect differences between those who have and have not had improved knee outcomes. Power analysis yielded a sample size of 48. Dropout rates are expected to be 30% based on institutional experience, owing to loss to follow-up and contralateral ACL rupture and graft failure, and as such 66 patients will be recruited. This is expected to take approximately 1–2 years of recruitment based on historical institutional caseloads.

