## Statistical methods

### Statistical methods for primary and secondary outcomes {20a}

Side-to-side difference in anterior tibial translation (the primary outcome), overall ACL-RSI, EQ5D-5L, Marx activity scales, IKDC and KOOS-QOL will be calculated as means, with measures of dispersion reported as standard deviation. Differences between groups will be reported as mean differences, with dispersion reported with confidence intervals. Data normality will be assessed with the Shapiro-Wilk test for continuous parametric assessment. Between-group comparisons, such as the primary outcome of mean difference in GNRB anteroposterior laxity at 2 years, will be assessed with independent samples *t*-tests. If data is found to be non-parametric in distribution, the Wilcoxon rank sum test will be utilised. Comparison of two dichotomous variables, such as return to sport rates and complication rates, will be performed with Fischer’s exact test. Repeated measures such as GNRB measures and mean PROMs will be assessed using mixed effects linear analysis. All tests are two-sided. A *p* value of <0.05 will be considered the cut-off for statistical significance.

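### Return to sport is tested with Fisher's exact test, which gives nothing to pool after multiple imputation, and the permitted single-imputation fallback can raise its false-positive rate to about 11% or more

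*Protocol article*

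**What the plan says.** Three parts of the protocol article bear on this point.

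- **Tests (Statistical methods, item 20a).** For binary outcomes: "Comparison of two dichotomous variables, such as return to sport rates and complication rates, will be performed with Fischer’s exact test". For continuous outcomes the default is the independent-samples t-test, with a switch: "If data is found to be non-parametric in distribution, the Wilcoxon rank sum test will be utilised". On error control: "All tests are two-sided" and "A *p* value of <0.05 will be considered the cut-off for statistical significance". Continuous outcomes are to be reported as mean differences with confidence intervals. No effect measure is named for binary outcomes.
- **Missing data (item 20c).** "Missing data will be quantified and if possible multiple imputation will be used; otherwise, simple imputation will be used". Neither the condition for multiple imputation nor the meaning of simple imputation is defined.
- **Expected loss (Sample size, item 14).** "Dropout rates are expected to be 30% based on institutional experience, owing to loss to follow-up and contralateral ACL rupture and graft failure".

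The Outcomes section (item 12) says where the binary data come from. Return to sport is self-reported in the questionnaire sent with the PROMs. Complications are taken from review of the medical record at 2 years.

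**The concern.** Rubin's rules combine an estimate and its standard error from each imputed dataset. Fisher's exact test as named supplies neither. An analyst who follows the methods section for return to sport therefore has no quantity to pool, and the missing-data section allows a single imputation instead.

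A single imputed dataset is analysed as if all 33 participants per arm had been observed. When the filled-in values come from the same arm, the test overstates the information available and repeats any chance difference between the observed arms. The false-positive rate then exceeds 5%, and at 30% missing the excess is large. Because simple imputation is undefined, the method could also be chosen after the data are seen.

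At stake is the inference on a named secondary outcome. If the fallback is used there, the continuous outcomes, including the primary one, are affected too.

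**Working it through.** **Inputs.** 66 randomised 1:1, so 33 per arm (Study setting; Sequence generation). Missing 30% (Sample size), about 0.30 × 33 = 9.9 per arm. Return-to-sport rate 55% (Background and rationale). Two-sided alpha 0.05. The plan gives no false-positive figure beyond that nominal 5%, so 5% is the benchmark. The simulations assume no true difference, data missing completely at random, and equal missingness in the arms.

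**Return to sport, Fisher's test, 55% rate.** Share of simulated trials with p < 0.05 (6,000 to 15,000 trials per setting; ranges are across separate simulations):

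- Complete data: 3.3–3.4%.
- Observed cases only: 3.3–3.4%.
- One random draw within arm: 10.7–11.3%.
- Each arm's majority category: 39.6–45.8%. The spread mainly reflects how ties between the categories are resolved.
- One random draw from both arms pooled: 3.3%.
- Majority category of both arms pooled: about 2%.
- Missing counted as not returned: 2.9%.
- Multiple imputation with 20 datasets, Rubin's rules: pooled risk difference 5.3–5.6%; pooled log odds ratio 4.6%.

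At other rates the single within-arm draw gives 10.8–11.4% (40% rate) and 9.1–9.6% (70% rate). The pooled risk difference gives 6.2% and 5.0%. With only 10% missing, the single within-arm draw at a 55% rate gives 6.0%, so the expected 30% loss is what makes this matter.

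**Dilution from pooled draws.** If a fraction m is missing and filled from both arms combined, the filled part carries no difference between arms. The expected difference is (1 − m)δ = 0.70δ. Counting missing as not returned gives 0.70p₁ − 0.70p₀ = 0.70δ as well.

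**Continuous outcomes, t-test, m = 0.30.** The test assumes an arm-mean variance of σ²/n.

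- Random within-arm draw: the true variance is about (σ²/n)[1/(1 − m) + m] = (σ²/n)(1.4286 + 0.30) = 1.7286 σ²/n. The effective critical value is 1.96/√1.7286 = 1.491, and 2[1 − Φ(1.491)] = 13.6%. Simulation: 13.3%.
- Within-arm mean: the true variance is σ²/[n(1 − m)], while the test uses about σ²(1 − m)/n. The effective critical value is 1.96 × 0.70 = 1.372, and 2[1 − Φ(1.372)] = 17.0%. Simulation: 16.5%.
- If the Wilcoxon switch applies: 12.6% (within-arm draw) and 30.7% (within-arm mean); with pooled draws or the pooled mean, 4.8% and 4.7%.

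**Complications.** The document gives no expected rate, so 5–20% is assumed. Even with a full 30% missing, the single within-arm draw gives 2.0% (5% rate), 5.2% (10%) and 8.4% (20%).

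**The case against.** A reader might infer that the plan forces return to sport and complications into single imputation and so doubles the error for both. The documents do not support that, for four reasons.

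- **No compulsion.** The condition on multiple imputation is undefined and is not tied to the choice of test. It may refer only to the amount or pattern of missing data. Multiple imputation is possible once a risk difference or log odds ratio is chosen. The text permits the fallback and, with the named test, invites it.
- **The method is not fixed.** Simple imputation need not be within arm. Pooled draws, or missing counted as not returned, stay at about 3%. This stands, but both shrink a true difference to about 70%, so the undefined term leaves a choice between inflated error and a diluted effect.
- **Complications differ.** They come from record review, and two listed causes of the 30% dropout, graft failure and contralateral rupture, are themselves recorded complications. The 30% therefore does not carry over, and the simulated error does not double at any assumed rate.
- **A workable binary analysis remains.** Fisher's test on observed cases is valid under the simulated missingness (3.3–3.4%), so removing the fallback does not leave return to sport without an analysis.

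Two further limits apply to continuous outcomes. The rank test concerns only non-normal continuous data; the t-test's mean difference can be pooled, and the planned mixed model for repeated measures can use incomplete records. The t-test is nevertheless the method named for the primary 2-year comparison, and the fallback sentence covers it. A reader might also fear that the normality check would select different tests in different imputed datasets, but the protocol does not say the check is repeated in each one.

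Finally, the imputation model and number of imputations may properly sit in a statistical analysis plan. Their absence is no part of this point, which rests on the test and fallback that the protocol does state.

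**Conclusion.** The point holds for self-reported return to sport. The protocol names a test that gives nothing to pool and permits an undefined single imputation while expecting 30% dropout. If the imputation is done within arm, the false-positive rate rises from a nominal 5% to about 11%, or about 40–46% with majority filling. A pooled, multiply imputed risk difference stays at about 5–6%. The same understated variance gives about 13–17% for the t-test on continuous outcomes if the fallback is used within arm.

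The size depends on within-arm imputation, a return rate near 55%, 30% missing completely at random and equal loss in the arms. It does not extend to complications. The change is worth making because the fallback can produce a wrong result and is cheap to replace.

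**What to change.** - In the missing-data section (item 20c), delete the clause that falls back to simple imputation.
- In the statistical methods section (item 20a), analyse return to sport as a risk difference with 95% CI (binomial model, or logistic regression with standardisation), estimated in each multiply imputed dataset and pooled by Rubin's rules.
- For continuous outcomes with missing values, pool the mean difference from a linear model.
- Keep Fisher's exact test for complications, on the understanding that record review leaves them essentially complete or that events are rare.

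The cost is about two sentences and standard software. The downside is that the model-based test is slightly less exact than Fisher's: about 5–6% false positives in simulation (6.2% at a 40% rate), against 3.3–3.4% for Fisher's test on complete data at a 55% rate.
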